# Open hemorrhoidectomy under local anesthesia versus saddle block in western Uganda: a study protocol for a prospective equivalence randomized, double-blind controlled trial

**DOI:** 10.1186/s13063-022-06636-8

**Published:** 2022-08-13

**Keywords:** Third- or 4th-degree hemorrhoids, Local anesthesia, Saddle block, Open hemorrhoidectomy, Uganda

## Abstract

**Background:**

While open hemorrhoidectomy under local anesthesia has been shown to be more cost-effective with shorter operation times and lower complication rates, local anesthesia is still not considered as a first-line technique in low-income countries like Uganda. The objective of this trial is to compare open hemorrhoidectomy using local anesthesia versus saddle block among patients with primary uncomplicated 3rd- or 4th-degree hemorrhoids in western Uganda.

**Methods:**

The protocol for a prospective equivalence randomized, double-blind controlled trial was conducted among patients with primary uncomplicated 3rd- or 4th-degree hemorrhoids. Recruitment was started in December 2021 and is expected to end in May 2022. Consenting participants who require open hemorrhoidectomy indicated at Kampala International Teaching Hospital, Uganda, will be randomized into two groups of 29 patients per arm.

**Discussion:**

The primary outcome of this study is to compare the occurrences of postoperative pain following open hemorrhoidectomy using the visual analog scale in an interval of 2, 4, and 6 h and 7 days postoperatively. Furthermore, the mean operative time from the induction of anesthesia to the end of the surgical procedure as well as the cost-effectiveness of the 2 techniques will be assessed in both groups. Open hemorrhoidectomy under local anesthesia has the potential to offer benefits to patients but most importantly expediting return to baseline and functional status, shorter hospital stay by meeting the faster discharge criteria, and reduction in costs associated with reduced length of stay and complications.

**Trial registration:**

Pan African Clinical Trials Registry PACTR202110667430356. Registered on 8 October 2021

## Introduction

Hemorrhoids, the most prevalent anal disease, are defined as collections of submucosal, fibrovascular, arterio-venous sinusoids that are part of the anorectum [1]. Clinically, hemorrhoids are expressed by bright red bleeding from the rectum with mucous discharge, perianal irritation and pain, prolapse of the hemorrhoidal cushions, bulging masses, soiling, and non-hygiene [1]. The paradigm about the treatment of hemorrhoids has changed over the years, and many options have been reported about hemorrhoid surgery [2]. These options range from conservative treatment (dietary and sclerotherapy) to surgical methods like band ligation and excision according to the grade of hemorrhoids [2, 3]. The classification by Banov L et al., grade III and IV hemorrhoids are amenable to surgical treatment, and open hemorrhoidectomy is effective and seems to be the most common technique for grade III and IV hemorrhoids [4, 5]. Surgical treatment is the only truly curative method of hemorrhoidal disease. This is indicated in patients to whom conservative measures have failed and for those who have developed complications. Of the several surgical techniques, the Milligan-Morgan hemorrhoidectomy is still considered the treatment of choice, since it is the most radical one and it has the best results [6]. One of the major problems associated with the technique remains postoperative pain. Studies reported severe pain occurred in 20–40% of patients [6, 7].

Local anesthesia (LA) is adequate for the majority of anal surgical procedures [8]. LA produces sensory and motor blockade in the peri-anal region with an effect on peripheral nerve endings and therefore produces varying and unpredictable degrees of anal canal relaxation [8]. Operative time has been shown to be different according to the anesthetic technique used in terms of time saved during operation according to studies done by Kushwaha and Baghel with their colleagues comparing the use of LA versus spine and GA for open hemorrhoidectomy [2, 9]. Despite producing interesting results presented in the literature, LA has been increasingly questioned, as to whether it brings more benefits to selected patients [10]. It was found that open hemorrhoidectomy (OH) under general anesthesia (GA) or spine anesthesia (SA) showed a high-cost implication as compared to OH done under local anesthesia in different studies published [2, 10, 11].

Open hemorrhoidectomy in most low- and middle-income countries (LMICs) is performed under saddle block which requires a trained anesthetic provider and is associated with delays in the initiation of surgery, postoperative urinary retention, neural injury, direct nerve and spinal cord injury, cauda equina syndrome, epidural hematoma post-dural puncture headache, failed block, epidural abscess, and hematoma [2, 12, 13]. These complications increase the duration of hospital stay and morbidity [13]. The few numbers of anesthetic providers in developing countries like Uganda (0.05 per 100,000 population compared to 17.85 per 100,000 in the UK [14]) have been seen as a hindrance to access and performance of open hemorrhoidectomy especially at low-level facilities despite open hemorrhoidectomy being a very common surgical procedure [8]. The costs of anesthetic procedures have become an important factor in the selection of the best technique for benign anal surgeries [10]. Saddle block needs a trained anesthetist to administer the anesthesia in order to perform open hemorrhoidectomy and has been associated with a long hospital stay [2, 13] which increases the cost related to OH compared to OH done under local anesthesia [2, 3, 9, 10].

While open hemorrhoidectomy under local anesthesia has been shown to have lower complication rates and more cost-effective by saving anesthetics for other surgeries, it has been also found to increase patient turnover because of the shorter operative time [2, 7]. In spite of these benefits, LA is still not considered as a first-line technique in low-income countries like Uganda. To explore the applicability of LA for OH in a limited setting, a well-designed randomized controlled trial is needed.

## Study rationale

Sound knowledge of safe and cheaper surgical options is mandatory to inform policy decisions in a low-income country like Uganda where the health care system is already constrained by other surgical and obstetric emergencies. This study will not only be a benchmark for future research but will also influence future trends in managing uncomplicated 3rd- and 4th-degree hemorrhoids in low-income countries.

## Main objective

The main objective is to compare open hemorrhoidectomy using local anesthesia versus saddle block among patients with primary uncomplicated 3rd- or 4th-degree hemorrhoids in western Uganda.

## Specific objectives

The following are the specific objectives:i.To compare the occurrence of postoperative pain following open hemorrhoidectomy under local anesthesia versus open hemorrhoidectomy under saddle blockii.To compare the mean operative time for open hemorrhoidectomy under local anesthesia versus open hemorrhoidectomy under saddle blockiii.To compare the cost-effectiveness between open hemorrhoidectomy under local anesthesia and saddle block

## Hypothesis

There is no significant difference in the surgical outcome between the use of local anesthesia versus saddle block for open hemorrhoidectomy of uncomplicated 3rd- or 4th-degree hemorrhoids.

## Methodology

### Study design

This study will be a prospective equivalence randomized, double-blind controlled trial conducted in the department of surgery at Kampala International University Teaching Hospital (KIU-TH), western Uganda.

### Study area

The study will be conducted in KIU-TH in the operating theater and general surgery ward.

KIU-TH is a private nonprofit teaching hospital of Kampala International University located in Bushenyi district, south-western Uganda about 370 km from Kampala, the capital city of Uganda. The hospital has a bed capacity of 700. The hospital consists of outpatient departments (general and special), inpatient departments for surgery (general surgery and orthopedic), gynecology and obstetrics, internal medicine, and pediatrics. The department has five theater rooms with an average of 800 elective surgeries per year. The Department of General Surgery has 13 surgeons and 42 residents. There are 3 days per week for elective surgery. There are three anesthesiologists and six anesthetists. KIU-TH has a 4-bed intensive care unit (ICU) being managed by anesthesiologists.

### Study population

All patients were admitted to the surgical ward for elective hemorrhoidectomy during the study period.

#### Inclusion criteria

All patients:Aged between 18 and 65 yearsUncomplicated 3rd- and 4th-degree hemorrhoidsClassified by the American Society of Anesthesiologists (ASA) as I and IIMixed hemorrhoids with a bulging external component

#### Exclusion criteria

All patients with:Contraindication of spinal anesthesia (chronic backache and spinal deformities)Previous perianal surgeryA known history of allergy to local anestheticsBleeding disordersThird- and 4th-degree thrombosed hemorrhoidsActive inflammatory bowel diseasePregnant womenDocumented neoplasm situated distal aspect of the large bowel or rectumLiver diseases with portal hypertensionFailed anesthetic technique

### Sample size determination

The randomized control trial assumes a null hypothesis that the mean postoperative pain scores after hemorrhoidectomy using local anesthesia are not different from that done under saddle block by a clinically relevant amount. Since the primary outcome measure was a continuous variable (i.e., pain level measured using a visual analog scale), the formula for an equivalence design in randomized control trials by Zhong et al. [15] was used.$$\boldsymbol{N}=\mathbf{2}\times {\left\{\frac{{\boldsymbol{Z}}_{\mathbf{1}-\propto}+{\boldsymbol{Z}}_{\mathbf{1}-\boldsymbol{\beta}}}{\boldsymbol{\delta}}\right\}}^{\mathbf{2}}\times {\boldsymbol{S}}^{\mathbf{2}}$$

where

***N***sample size per group

***Z***_***1−α***_standard normal deviate for a two-sided test used in equivalence trials (1.96 for 95% confidence interval)

***δ***clinically admissible margin of equivalence design as a difference

***α***type I error associated with rejecting the null hypothesis when it is true; (0.05) for 95% confidence interval

***β***type II error associated with the alternative hypothesis, assumed to be 0.20 for a statistical power of 80%

**(1−*****β*****)**the probability of rejecting the null hypothesis when it is false, i.e., *Z*_1−*β*_ = 0.845 for statistical power of 80%

***S***^**2**^pooled standard deviation of both comparison groups

According to a similar randomized control trial that compared open hemorrhoidectomy under local anesthesia versus supine anesthesia at the Korle Bu Teaching Hospital in Ghana [16], the difference in the mean pain scores between the 2 groups was *δ* = 0.73; pooled standard deviation in the mean pain scores *S* = 1.9 (average of 2.356 for local anesthesia and 1.479 for supine anesthesia), an estimated sample size of 104 participants per group, was obtained. Since at the time of the proposed study, nothing was known about the mean pain score following OH under local anesthesia and the real difference in clinical outcome between the two techniques in Uganda, the sample size was adjusted using Slovin’s formula as detailed by Ellen [17] based on the hospital records, Kampala International University Teaching Hospital which registered an average of 33 cases of grade 3 or 4 hemorrhoids in a period of 6 months that corresponded to the intended data collection period; thus, a sample size of 26 participants per group was obtained which was increased to 29 participants in each arm, based on a rate of 10% in each arm to compensate for the loss to follow-up and non-responsiveness found.

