### Data processing and analysis plan

Data will be statistically analyzed using IBM Statistics SPSS for Windows 23.0. The primary outcome will analyze all randomized patients (on an intent-to-treat (ITT) basis) and per-protocol (PP) population. The mean pain scores at rest and their standard deviations will be computed and compared using one-way ANOVA tests. VAS will be stratified as ordinal (0 as no pain, 1–3 as mild, 4–6 as moderate, and 7–10 as severe); the significance of the difference in the mean scores between local and saddle groups will be determined by the Kruskall-Wallis (*H*) test at 95% confidence interval, regarding *p* < 0.05 as statistically significant; furthermore, the mean pain scores will be analyzed for significant differences in the area under the curve (AUC) for VAS (2-sample *t*-test). The mean operative time and standard deviation will be computed for each technique of open hemorrhoidectomy. Cross tabulation will be performed between the two open hemorrhoidectomy techniques for categorical cost-effective analysis. The difference in the means will be compared using the *t*-test and their corresponding two-tailed p-value, regarding *p* < 0.05 as statistically significant.

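### The sample-size section labels 1.96 as Z(1−α) with α = 0.05, although for equivalence it means 0.025 per one-sided test; its inputs give 107 per group, not 104, and 107 has about 60% power, not 80%

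*Protocol article*

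**What the plan says.** The article describes an equivalence trial and takes its sample-size formula from a source on equivalence designs: N per group = 2 × {(Z(1−α) + Z(1−β))/δ}² × S². Under Sample size determination the terms are defined as follows.

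- Z(1−α) is the "standard normal deviate for a two-sided test used in equivalence trials (1.96 for 95% confidence interval").
- α is the "type I error associated with rejecting the null hypothesis when it is true; (0.05) for 95% confidence interval".
- β is "assumed to be 0.20 for a statistical power of 80" percent, with Z(1−β) = 0.845.
- δ is the "clinically admissible margin of equivalence design as a difference". Its value comes from an earlier trial in Ghana, where "the difference in the mean pain scores between the 2 groups was *δ* = 0.73".
- S is 1.9, described as the "average of 2.356 for local anesthesia and 1.479 for supine anesthesia".

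From these inputs "an estimated sample size of 104 participants per group, was obtained". The same section then replaces that figure, by Slovin's formula and a 10% allowance for loss, with 26 and finally 29 per arm.

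Under Data processing and analysis plan, means are compared by t-test with a "two-tailed p-value, regarding" p < 0.05 as significant. ANOVA and Kruskal-Wallis tests are also listed. No interval is compared with a margin.

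**The concern.** Three statements about one term do not fit together: the subscript 1−α, the value α = 0.05, and the deviate 1.96. At α = 0.05, Z(1−α) is 1.645. The value 1.96 is Z(0.975), that is Z(1−α/2).

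For a two-sided test of difference this would be only a misprinted subscript. For equivalence it also misstates the error rate. The error that matters is declaring equivalence when the true difference is at or beyond the margin. A 95% interval required to lie inside the margin holds that error to at most 2.5%, not 5%.

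The formula also uses Z(1−β) undivided. When the true difference is 0, both one-sided tests must succeed, and each can fail. The type II error is then about 2β. So the 80% attached to this calculation needs checking, as does the 104.

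**Working it through.** **Inputs.** All are from Sample size determination: δ = 0.73, S = 1.9, Z(1−β) = 0.845, deviate 1.96.

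**Step 1: reproduce the stated 104.**

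N = 2 × ((1.96 + 0.845)/0.73)² × 1.9² = 2 × (3.8425)² × 3.61 = 106.6, so 107 per group.

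The stated 104 is within 3% of this but is not the result. Solving the formula for the deviate at N = 104 gives √(104/2) × 0.73/1.9 − 0.845 = 1.926, which is not a stated level. Other ways of forming S do not help:

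| S | How formed | N at 1.96 |
|---|---|---|
| 1.9 | as stated | 106.6 |
| 1.9175 | unrounded mean of 2.356 and 1.479 | 108.6 |
| 1.967 | root mean square of the two SDs | 114.3 |

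**Step 2: which deviate was used.** Putting 1.645 in place of 1.96 gives 84.0, far from 104. The stated figure therefore rests on 1.96, and the error lies in the label.

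**Step 3: what 1.96 means for equivalence.** The upper tail beyond 1.96 is 0.025. A 95% interval wholly inside ±δ is the same as two one-sided tests at 0.025 each.

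**Step 4: power if the true difference is 0** (normal approximation).

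Power = 2Φ(δ/SE − 1.96) − 1, with SE = S√(2/N).

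- N = 104: SE = 0.2635, power = 58%.
- N = 107: SE = 0.2598, δ/SE − 1.96 = 0.850, power = 60%.

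The general result is 2Φ(0.845) − 1 = 0.60: the printed formula delivers 1 − 2β, not 1 − β.

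**Step 5: size for 80% power.** Replace Z(1−β) by Z(1−β/2) = Z(0.90) = 1.2816:

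N = 2 × ((1.96 + 1.2816)/0.73)² × 1.9² = 142.4, so about 143 per group.

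**Step 6: the planned 29 per arm.** At S = 1.9, SE = 1.9 × √(2/29) = 0.499. With t on 56 degrees of freedom, the half-width of the 95% interval is 1.00 and that of a 90% interval is 0.83. Both exceed 0.73, so neither could lie inside the margin, whatever difference is observed.

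**The case against.** The strongest defence is that this is one wrong subscript. On the ordinary two-sided convention, 0.05, 1.96 and 95% agree, and the article ties α itself to the 95% interval. The null hypothesis in that section is also worded as no relevant difference, for which a two-sided 0.05 would be the natural label. The choice is conservative: a 95% rule satisfies a 5% ceiling as well, and 1.96 gives a larger sample than 1.645. Finally, 104 does not set the trial's size.

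Most of this stands. The intended level is not in doubt, and false equivalence is not inflated. What remains is that the design and the formula are for equivalence. Under them, 0.05 is not the error rate of the conclusion, 104 is not what the inputs give, and 80% is not the power.

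A reader might go further and infer that the text leaves a 90% interval open, so that a borderline result could be called equivalent on one reading and not on the other. The article does not support that. It never mentions 1.645 or a 90% interval; 95% is the only interval named, always with two-sided or two-tailed wording; and 104 rests on 1.96. Step 6 shows that at the planning SD and 29 per arm the two levels would not even give different answers.

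**Conclusion.** The point holds as a conservative labelling error with two wrong figures attached. The level used is 0.025 for each one-sided test, not the stated 0.05. The per-group size from the printed inputs is 107, not 104. Its power for equivalence at a true difference of 0 is about 60%, not 80%, and 80% would take about 143. If the true difference is not 0, power is lower still.

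The analysis section matters here because it states only difference tests. A non-significant two-tailed p-value does not show equivalence at any level, so the intended 95% level does its work only if it is tied to an interval and the margin.

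These results assume that the margin is ±0.73 VAS points, that the SD is 1.9 in both arms, and that means are compared on that scale. The primary outcome is an area under the curve for VAS, whose scale the article does not give, so the margin and SD may need restating for it. The correction does not alter the larger limitation that 29 per arm, at SD 1.9, cannot place a 95% interval inside 0.73.

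**What to change.** 1. In Sample size determination, write the deviate as Z(1−α/2) = 1.96 and state that this is one-sided 0.025 for each of the two one-sided tests.
2. In Data processing and analysis plan, add: equivalence is concluded only if the two-sided 95% confidence interval for the difference lies wholly within the margin, and a non-significant two-tailed p-value is not taken as evidence of equivalence.
3. Restate 104 as 107 per group with power of about 60% at a true difference of 0, or give about 143 as the size for 80% power. Keep the existing account of how 29 per arm was reached, so that the gap is visible.

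The cost is a few sentences, with no change to enrolment. An interim analysis was done on 10 March 2022, so the change should be dated and made before the final analysis. It keeps the 95% level already printed, so it need not look like a choice made from the data.

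The price of candour is that the article will show, in its own figures, a planned size well below what its equivalence aim requires.

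### The equivalence margin of 0.73 is an earlier trial's observed difference, and the formula leaves 104 per group short of 80% equivalence power; at 29 per arm that power is essentially zero

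*Protocol article*

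**What the plan says.** All of this is in the Sample size determination section of the protocol article unless another section is named.

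- Delta is defined as the "clinically admissible margin of equivalence design as a difference".
- The value entered comes from an earlier trial in Ghana, where "the difference in the mean pain scores between the 2 groups was" 0.73. No clinical argument for 0.73 and no other margin is given.
- The alpha term is labelled Z(1-alpha) with alpha 0.05, and is described as the "standard normal deviate for a two-sided test used in equivalence trials (1.96 for 95% confidence interval").
- Beta is 0.20, and the power term is Z(1-beta), "0.845 for statistical power of 80" per cent.
- S is called a pooled standard deviation and set to 1.9, the "average of 2.356 for local anesthesia and 1.479 for supine anesthesia".
- From these inputs "an estimated sample size of 104 participants per group, was obtained". That number is then cut to 26 per group with Slovin's formula and raised to 29 for losses.
- The Primary outcome variable section makes the area under the curve (AUC) of the VAS the primary measure.
- The Data processing and analysis plan section compares groups with ANOVA, Kruskal-Wallis and t-tests at p < 0.05. It does not mention the margin.

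**The concern.** An equivalence margin says how large a difference can be and still not matter to patients. A difference observed in an earlier trial estimates how far apart the treatments are. The article defines delta as the first and fills it with the second. If the earlier trial's estimate is right, the true difference lies exactly on the margin, and no sample size would give a reasonable chance of showing equivalence.

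The second issue is the power term. Equivalence requires the interval to clear both bounds, so with a true difference of zero the type II error has to be shared between them. The formula gives all of beta to one bound. The stated 80% is then the power for one bound and is not reached for two.

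At stake are a margin with no stated clinical meaning in a trial labelled an equivalence trial, and a power figure that its own inputs do not support.

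**Working it through.** **Inputs from the article.** Margin 0.73; S = 1.9; SDs 2.356 and 1.479; z = 1.96; Z(1-beta) = 0.845; 104 per group from the formula; 29 per arm planned.

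**Assumptions.** The article states no true difference. Zero is used as the most favourable case, and other values are shown. Because the article labels its term Z(1-alpha) with alpha 0.05 but uses 1.96, both z = 1.96 (95% interval) and z = 1.645 (90% interval) are shown.

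**1. The article's own figure.** N = 2 × ((1.96 + 0.845)/0.73)² × 1.9² = 106.6, so 107. This is within 3% of 104, and the gap is not raised as an error.

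**2. What that formula delivers.** SE at 104 per group = 1.9 × √(2/104) = 0.2635. With a true difference of zero:

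- One bound: Φ(0.73/0.2635 − 1.96) = Φ(0.81) = 0.79. The power of a two-sided superiority test for a difference of 0.73 is also 79%.
- Both bounds, 95% interval: 2 × 0.791 − 1 = 0.58 (t-based simulation 57.5%).
- Both bounds, 90% interval: 2 × Φ(0.73/0.2635 − 1.645) − 1 = 0.74 (simulation 73.5%).

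With 107 per group the figures are 60% and 76%.

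**3. Other true differences, 104 per group.** Power = Φ((0.73 − d)/SE − z) + Φ((0.73 + d)/SE − z) − 1.

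| True difference d | 95% interval | 90% interval |
|---|---|---|
| 0 | 58% | 74% |
| 0.2 | 46% | 61% |
| 0.365 (half the margin) | 27% | 39% |
| 0.73 (earlier trial) | 2.5% | 5% |

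The last row is the one-sided alpha, and a larger n does not raise it.

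**4. Size needed for 80%, true difference zero.** N = 2 × ((z + 1.2816)/0.73)² × S², where 1.2816 = Z(1-beta/2).

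- S = 1.9: 142.4, so 143 (95% interval); 116.03, so 117 (90% interval).
- Variance-pooled S = √((2.356² + 1.479²)/2) = 1.967, taking equal groups in the earlier trial: 152.6, so 153; 124.4, so 125.

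With S = 1.967, power at 104 is 53% or 70%. The choice of SD is a minor part of the shortfall.

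**5. The planned size.** SE at 29 per arm = 1.9 × √(2/29) = 0.499. Half-width = 1.96 × 0.499 = 0.98 (95%) or 1.645 × 0.499 = 0.82 (90%). Both exceed 0.73, so an interval of the expected width cannot fit between −0.73 and +0.73 even when centred on zero. Simulated power, allowing for chance variation in the estimated SD, is about 0.01% (95%) and 0.5% (90%).

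**The case against.** The strongest reply is that 104 was never the enrolment target. The article dropped it for 29 per arm, so correcting beta changes nothing in the trial as run. That is fair as to materiality. The cut to 29 is the larger problem, and the figure that matters for this trial is the one in step 5. It does not rescue the margin, which is the only one given, or the 80% attached to the formula.

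A reader might infer that the margin decides the trial's conclusion. As written it does not. The analysis section relies on significance tests, and the Hypothesis section speaks of no significant difference, so the margin enters only the sample-size formula. The link between margin and conclusion has to be added.

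A reader might also infer that at least 143 per group is required. That holds only for the 95% interval. With a 90% interval and S = 1.9 the requirement is 117, which is 13 above 104.

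Two further inferences go too far. The article does not claim 80% power for 29 per arm; the 80% belongs to the calculation that gave 104. Nor do the documents show that 0.73 is clinically too wide or too narrow. They show only that no clinical reason was given for it.

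**Conclusion.** The point stands in two parts. First, the section contradicts itself: it defines delta as a clinical margin and fills it with an observed effect. This needs no calculation. Second, the 80% power is not met for two-bound equivalence under either reading of alpha. Power at 104 per group is 58% or 74% with SD 1.9, and 53% or 70% with the variance-pooled SD. These figures rest on an assumed true difference of zero, and any other value lowers them. The size needed for 80% with a margin of 0.73 is 117 to 153 per group, depending on interval level and SD. At 29 per arm the trial has essentially no chance of showing equivalence within 0.73.

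**What to change.** Rewrite the sample-size paragraph and add one sentence to the analysis section.

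1. Stop presenting 0.73 as a clinical margin. Cite it only as prior evidence of the effect.
2. State a margin justified on clinical grounds in the units of the primary endpoint: AUC of the VAS, or mean VAS if that is the endpoint analysed. The 0.73 and 1.9 are in mean-score units and do not carry over to AUC.
3. Have the margin set by people blind to the interim results, and dated before the final analysis. The Interim analysis section provides for evaluating the primary outcome and reports that the analysis was done on 10 March 2022. The Trial status section reports 45 of 58 patients registered by 7 April 2022. A margin chosen with knowledge of those results would be post hoc.
4. In the analysis section, state the confidence level and compare the interval for the group difference with the margin.
5. Restate the calculation with Z(1-beta/2) and the variance-pooled SD, showing the 117 to 153 range for 0.73. Withdraw the 80% statement, and report the true power or expected interval half-width at 29 per arm.

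This adds no patients. The cost is that the stated figures become less favourable.

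### The printed 104 per group does not follow from the plan's own formula: its inputs give 107, a properly pooled SD gives 115, and 104 carries about 76% power by that formula, not 80%

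*Protocol article*

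**What the plan says.** All of this stands in the Protocol article, Sample size determination.

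- The formula is N per group = 2 × {(Z for alpha + Z for power)/δ}² × S².
- Z for alpha is the "standard normal deviate for a two-sided test used in equivalence trials (1.96 for 95% confidence interval".
- The type II error is "assumed to be 0.20 for a statistical power of 80" percent, with the matching deviate given as "0.845 for statistical power of 80" percent.
- δ is defined as the "clinically admissible margin of equivalence design as a difference" and set to 0.73, the difference in mean pain scores seen in a cited randomised trial from Ghana.
- The variability term is described as the "pooled standard deviation of both comparison groups". Its value, S = 1.9, is then explained as the "average of 2.356 for local anesthesia and 1.479 for supine anesthesia), an estimated sample size of 104 participants per group, was obtained".

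The next sentence reduces the figure to 26 per group with Slovin's formula and raises it to 29 per arm for a 10% loss. Randomization and blinding describes equal allocation, with half the envelopes for each arm.

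**The concern.** The article prints the formula, every input and the result, so the result can be checked directly, and it does not agree with the inputs. The article also says how S was obtained, and that method is not pooling. Averaging SDs understates the pooled SD whenever the two differ; here the variances differ by a factor of about 2.5 (5.551/2.187).

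The figure of 104 is the only sample size in the article that rests on the stated 80% power. A reader will use it as the yardstick for how far the planned 58 patients fall short, and may reuse S = 1.9 to work out the precision of the enrolled sample.

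**Working it through.** **Inputs** (all from Sample size determination): δ = 0.73; deviates 1.96 and 0.845; arm SDs 2.356 and 1.479; printed S = 1.9; printed N = 104 per group.

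**Step 1. The plan's own figure.** The multiplier of S² is 2 × (2.805/0.73)² = 29.529. With S = 1.9, N = 29.529 × 3.61 = 106.6, so 107. This is close to 104 but not equal to it. An exact 104 would need S of about 1.877. One-sided 5% gives 84; replacing 0.845 by the deviate for beta/2 gives 143 with 1.96 and 117 with the one-sided 5% deviate. None comes closer to 104 than 107 does.

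**Step 2. What S should be.** With n per arm, the variance of the difference in means is (s₁² + s₂²)/n. The formula uses 2S²/n. The two agree only if S² is the mean of the two variances:

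- average of the SDs: (2.356 + 1.479)/2 = 1.9175, printed as 1.9
- pooled SD: √[(5.551 + 2.187)/2] = 1.967

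**Step 3. N per group and where the gap arises.**

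| S | N by the formula | Rounded up | Step |
|---|---|---|---|
| printed result | – | 104 | – |
| 1.9 | 106.6 | 107 | +3, unexplained arithmetic |
| 1.9175 | 108.6 | 109 | +2, rounding of S |
| 1.967 | 114.3 | 115 | +6, averaging SDs instead of variances |

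The total is 11 per group (11/104 = 10.6%). Using 1.97 in place of 1.967 gives 114.6, again 115.

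**Step 4. Power by the plan's formula**, Φ(0.73/(S√(2/n)) − 1.96):

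- n = 104, S = 1.9: 79.1%
- n = 104, S = 1.967: Φ(2.676 − 1.96) = 76.3%
- n = 115, S = 1.967: Φ(2.814 − 1.96) = 80.4%

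**Step 5. Power for a two-sided equivalence conclusion** (95% interval inside ±0.73, true difference 0), 2Φ(·) − 1 with the same argument:

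- n = 104, S = 1.967: 2 × 0.763 − 1 = 52.6% (58.2% with S = 1.9)
- n = 115, S = 1.967: 2 × 0.8035 − 1 = 60.7%

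**Step 6. The enrolled size, 29 per arm.** Power by the plan's formula is 29.2% with S = 1.967 and 31.0% with S = 1.9. The expected 95% half-width, 1.96 × S × √(2/29), is 1.01 VAS points against 0.98.

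**Step 7. Does the target move?** The article does not show how 26 was reached. Assuming a finite-population correction to 33 cases, n/(1 + (n − 1)/33), 104 becomes 25.2 and 115 becomes 25.8. Both round up to 26, and 26 × 1.1 = 28.6 gives 29.

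**The case against.** The strongest reply is that nothing in the trial depends on 104. It was replaced by 29 per arm, and Trial status reports 45 of 58 patients already registered. Against either 104 or 115, 29 per arm is plainly far short. The Study limitations section itself concedes that a sample-size formula gave only a rough figure lacking statistical power. The article states no precision for 29 per arm, and 1.01 against 0.98 VAS points is negligible. All of this stands, and it is why the point is minor.

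A second reply is that the arm sizes of the cited trial are unknown, so its pooled SD weighted by degrees of freedom could differ. If the local-anesthesia share lay between 40% and 60%, that SD would run from 1.88 (N = 105) to 2.05 (N = 125). This does not rescue 104: the article says it averaged the SDs and used 1.9, and for a trial with equal allocation the formula needs 1.967 whatever the source arm sizes were.

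A third reply is that the input is itself uncertain. The SDs describe mean pain scores at no stated time point, while the primary outcome is an area under the VAS curve. That is fair: 1.967 is the right combination of the article's two SDs, not a demonstrated SD of the primary endpoint.

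A reader might also infer more than the article supports:

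- That the wrong SD explains the whole gap of 11. It does not; averaging SDs accounts for 6.
- That 1.9175 was shaded downwards. Writing it as 1.9 is ordinary one-decimal rounding.
- That correcting S calls for more patients. On the reconstruction above, the target stays at 29.
- That 115 would give 80% power for equivalence. It would not, as step 5 shows.

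**Conclusion.** The point holds as a minor error in stated figures. The printed 104 per group is not what the formula gives from the printed inputs (107), and the S it uses is an average of SDs where a pooled SD is defined (115 with S = 1.967). By the plan's formula 104 per group has about 76% power, not 80%.

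These figures take the article's δ, deviates and arm SDs as given and assume equal allocation. They do not endorse the formula: with a true difference of 0, power for a two-sided equivalence conclusion is about 53% at 104 and 61% at 115. The use of an observed difference as the margin, the power term in the formula and the reduction to 29 per arm are separate and larger questions, not judged here. That the target stays at 29 rests on an assumed reconstruction of the reduction step.

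**What to change.** In Sample size determination:

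1. Replace S = 1.9 by S = 1.97, described as the square root of the mean of the two arm variances.
2. Either restate the formula result as 115 per group, or keep 104 and give its power as about 76%.
3. Add that this is power by the formula as printed, and that it does not deliver 80% for a two-sided equivalence conclusion (about 53% at 104 and 61% at 115 per group, true difference 0). Without this sentence, printing 115 beside 80% would still mislead.
4. Use S = 1.97 for any power or precision given for the enrolled 29 per arm: about 29% by the plan's formula and an expected 95% half-width of about 1.01 VAS points.

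The cost is a few corrected figures and one added sentence. The stated figures become slightly less favourable. No patients, visits or procedures are added and the enrolment target does not change.
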